### Secondary outcome measures

In order to identify implementation difficulties of TUPAC counselling guidelines among dental providers, a Theoretical Domain Questionnaire (TDQ) will be developed according to the theoretical framework published by Michie *et al. *[19]. Additionally, the TDQ will be based on the Finnish Current Care guidelines on TUPAC counselling (six *A*s approach). We will select items from published literature and create new items to cover different aspects of the guideline recommendation and theoretical domains. The aim of the TDQ development is to create a tool to assess the mediators and theoretical explanations for implementation difficulties.

Adherence to the TUPAC counselling guidelines will be assessed by a previously used and validated instrument [20,21] covering the six *A*s approach [12]. A similar questionnaire will be developed for patients to receive more objective results of dental providers' implementation of TUPAC guidelines. For determining participants' tobacco use, derivation of smoking index will be used (additional file 5).

### Trial design

After developing the TDQ, we will conduct a provider baseline survey and EDR audit to measure the baseline adherence to TUPAC counselling guidelines and prevailing implementation difficulties among our sample. Based on identified implementation difficulties, we will use relevant behaviour-change theories and techniques in designing two interventions to enhance TUPAC guideline implementation. In selecting relevant intervention techniques, we will use a matrix of theoretical domains and 35 behaviour-change techniques [19] (Figure 1). Finally, we will test these interventions using a cluster randomised controlled trial (Figure 2).

Dental providers usually work in only one clinic, but when this is not the case, chief dental officers will merge two or more clinics into one cluster to reduce contamination across participants. After merging clinics and forming clusters, chief dentists will provide a concealed sequence of clusters to investigators who will allocate clusters randomly to (a) control, (b) low-intensity intervention, or (c) high-intensity intervention groups (Figure 2) by drawing lots. Allocation will be concealed from the investigators until data collection has been conducted. Investigators, patients, outcome assessors, and study statistician will be blinded to group allocation until the statistical analysis has been completed. Due to the nature of the study setting, it is not possible to blind the dental providers for group allocation. The success of blinding will not be evaluated.

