## Methods

### Participants

All dentists and dental hygienists employed by the Finnish municipal health centres of Vaasa (9 clinics) and Tampere (28 clinics) will be invited to participate, except two clinics' staff in Tampere (emergency and special treatment clinic) and one clinic's staff in Vaasa (undergraduate education clinic) (Figure 2). Implementing TUPAC counselling interventions in those excluded clinics would not be feasible. Participants meeting the inclusion criteria will receive the explanatory statement of the study (additional files 1 and 2), consent form (additional file 3), and instructions to participate (additional file 4). The survey will be conducted using either a web-based survey http://www.surveymonkey.com or a more traditional paper form survey. Strategies to promote response rates among dental providers include offering two movie tickets (value about €10 per ticket) for participation. We will also send two reminder letters (the first reminder one week and the second two weeks after the first request to respond) to nonrespondents.

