### Sample size

There is a scarcity of recent national data regarding the implementation of TUPAC counselling guidelines reported by dental providers. Hence, we conducted our sample size calculations based on population reports collected by the National Institute for Health and Welfare from a random sample (n = 5,000) of Finnish adults [8]. The data showed that 10.5% of surveyed tobacco users who visited the dentist at least once during the past 12 months had received any TUPAC counselling [8]. As our primary aim is to compare the implementation of TUPAC counselling guidelines between control versus two intervention groups, sample size is calculated using the following assumptions: Our aim is to increase the proportion of counselled patients from 10.5% (control) to 33% in the first (low-intensity) intervention group and to 63% in the second (high-intensity) intervention group, as validated by dental record audit. To achieve 80% power, with a two-sided 5% significance level with an estimated intra-class correlation of 0.02, we will need totally 72 participants and 12 clusters with an average of six participants per cluster. Assuming a baseline response rate of 76%, we will need a sample of 95 dental providers.

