### Trial update

The baseline survey (background information, self-reported guideline implementation, the theory-based assessment of implementation difficulties) and the EDR audit of the sample were conducted in September 2009. Of those eligible, 76.8% participated (n = 73/95). The study participants were fairly representative of municipal dental providers (Table 1). Participating dentists had practiced more clinical years on average (22.4 years) compared to dental hygienists (10.2 years; *p *< .001) and reported higher lifetime tobacco abstinence (72.2%) than dental hygienists (21.1%; *p *< .001) (Table 2). Regular tobacco use was uncommon in both provider groups. More dental hygienists had received undergraduate education on TUPAC counselling compared to dentists (84.2% versus 24.1%; *p *< .001). The results of the self-reported guideline implementation, theory-based assessment of implementation difficulties, and EDR audit will be reported elsewhere.

**Table 1 T1:** The comparison of gender and mean age of study participants, nonrespondents, and municipal dental practitioners in Finland

	Participants		Nonrespondents		Total		Municipal dentists
	Dentists (n = 54)	Hygienists (n = 19)	Dentists (n = 19)	Hygienists (n = 3)	Dentists (n = 73)	Hygienists (n = 22)	Dentists* (n = 2,002)
Female (%)	81.5	100	68.4	100	78.1	100	77.4
Mean age, years (SD)	48.7 (9.1)	37.3 (9.5)	51.1 (9.3)	46.7 (16.7)	48.9 (9.5)	38.6 (10.7)	49.5 (8.7)

*Finnish Dental Association statistics 2010. No national data available for dental hygienists.

**Table 2 T2:** Participant characteristics at baseline

	Dentists (n = 54)	Dental hygienists (n = 19)	*p *value*	Total (n = 73)
Response rate (%)	74.0	86.4	.27	76.8
Years practised (SD)	22.4 (9.1)	10.2 (7.6)	<.001	19.2 (10.2)
Mean clinical hours per week (SD)	28.0 (7.4)	31.1 (8.2.)	.14	28.8 (7.7)
Tobacco use (%)				
Never	72.2	21.1	<.001	58.9
Gave up 1 to 12 months ago	3.7	0	.40	2.7
Occasional	1.9	10.5	.10	4.1
Regular	3.7	5.3	.71	4.1
Received undergraduate education on tobacco use prevention or cessation counselling (%)	24.1	84.2	<.001	39.7
Received continuing education on tobacco use prevention or cessation counselling (%)	37.0	31.6	.67	35.6

**p *values calculated using chi-square and *t*-tests.

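### About 12 clusters from two cities go to three arms by drawing lots, with no stratification by city described; this leaves avoidable chance imbalance and some lost precision

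*Protocol article*

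**What the plan says.** The Participants section says that all dentists and hygienists "employed by the Finnish municipal health centres of Vaasa (9 clinics) and Tampere (28 clinics) will be invited to participate". Two Tampere clinics and one Vaasa clinic are excluded, which leaves 26 and 8.

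Under Trial design, clinics that share staff are merged into clusters. Then "chief dentists will provide a concealed sequence of clusters to investigators", and it is the investigators "who will allocate clusters randomly to (a) control, (b) low-intensity intervention, or (c) high-intensity intervention groups (Figure 2) by drawing lots". The article describes no stratum, matching or balancing constraint and states no allocation ratio.

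The Sample size section states that "we will need totally 72 participants and 12 clusters with an average of six participants per cluster".

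The same Trial design section puts a baseline measurement before the trial stage: "we will conduct a provider baseline survey and EDR audit to measure the baseline adherence to TUPAC counselling guidelines". The Trial update confirms that this has happened: "the EDR audit of the sample were conducted in September 2009". The record audit is also how the primary outcome is measured (Primary outcome measures).

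The Data analysis section plans adjusted generalised linear models and modified t-tests for the intervention effects. It names no covariates.

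**The concern.** With about four clusters per arm, one draw of lots can easily leave the arms with different mixes of the two cities. The cities run separate health centres; the Ethical review section shows that permission came from a different authority in each. The primary outcome depends on providers entering procedure codes, and the Discussion concedes that they may not always do so. Local habits in counselling or coding could therefore differ by city. If they do, an unequal city mix moves an unadjusted arm contrast. An analysis that adjusts for city afterwards removes the shift but pays for the imbalance in variance.

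City is known for every cluster, and the baseline audit is complete. Both could be used at the draw for very little effort, in a trial whose Discussion calls its own sample relatively small.

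**Working it through.** **Inputs from the article.** 72 participants / 6 per cluster = 12 clusters, as stated. The 73 actual participants give 73 / 6 = 12.2, which is consistent. Whether 72 follows from the power assumptions is a separate question and does not affect this point. Eligible clinics: 9 - 1 = 8 in Vaasa and 28 - 2 = 26 in Tampere.

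**Assumptions.** Equal arms, 12 / 3 = 4 clusters each. Number of Vaasa clusters V: if merging is proportional, 12 x 8/34 = 2.8, so V = 3; range shown, 2 to 6.

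**Chance of imbalance.** With x1, x2, x3 Vaasa clusters in the three arms (sum V), the probability of a split is C(4,x1) C(4,x2) C(4,x3) / C(12,V).

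For V = 3 there are C(12,3) = 220 equally likely placements:
- One Vaasa cluster in each arm: 4 x 4 x 4 = 64. So P(some arm has none) = 1 - 64/220 = 70.9%.
- Control has none: C(8,3)/220 = 56/220 = 25.5%.
- Control and high-intensity differ by two or more: 2 x (6 x 4) for a 2-versus-0 split with the third cluster in low-intensity, plus 2 x 4 for a 3-versus-0 split, = 56; 56/220 = 25.5%.

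For V = 4 there are C(12,4) = 495 placements:
- All arms have at least one: 3 x (6 x 4 x 4) = 288. So P(some arm has none) = 207/495 = 41.8%.
- Control has none: C(8,4)/495 = 70/495 = 14.1%.

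| Vaasa clusters | Some arm has none | Control and high-intensity differ by 2 or more | Some arm all Vaasa |
|---|---|---|---|
| 2 | 100% (unavoidable) | 18.2% | 0 |
| 3 | 70.9% | 25.5% | 0 |
| 4 | 41.8% | 27.9% | 0.6% |
| 5 | 21.2% | 30.3% | 3.0% |
| 6 | 9.1% | 31.6% | 9.1% |

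**What an imbalance does without adjustment.** A difference of two clusters out of four shifts the contrast by 2/4, that is, half of whatever city difference exists.

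**What it costs with adjustment for city.** In a cluster-level linear model, the variance of the high-intensity versus control contrast is multiplied by 1 + (d²/S)/0.5. Here d is the difference in the proportion of Vaasa clusters and S is the sum over arms of x(4 - x)/4. For V = 3:
- 1/1/1 split: d = 0, factor 1.00.
- 2 versus 0, third cluster in low-intensity: d = 0.5, S = 1 + 0.75 = 1.75, factor 1.29.
- 2 versus 1, or 1 versus 0 with two in low-intensity: d = 0.25, S = 1.75, factor 1.07.
- 3 versus 0: d = 0.75, S = 0.75, factor 2.50.
- All three in low-intensity: factor 1.00.

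Weighted mean: (48 x 1.286 + 96 x 1.071 + 8 x 2.5 + 68 x 1) / 220 = 1.15. Lots within city give 1/1/1 and a factor of 1.00 every time.

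**Cost and gain of the covariates.** Residual degrees of freedom at cluster level are 12 - 3 = 9, or 7 with two covariates. The squared two-sided 5% critical t rises by (2.365/2.262)² = 1.093, about 9%. A baseline score with correlation r to follow-up multiplies the residual variance by 1 - r². Break-even is 1 - r² = 1/1.093 = 0.915, so r is about 0.29. At an assumed r of 0.5 the net factor is 0.75 x 1.093 = 0.82.

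**The case against.** Simple cluster randomisation is valid. The estimate is unbiased over repeated draws, so nothing here is an error of inference. This is also a condensed article: it does not say that the lots were pooled across cities, its flowchart is not shown, and a fuller protocol might stratify. That stands as a caveat. But the article does set out the allocation step by step, and a restriction on the draw would belong in that description.

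Three stronger readings are tempting, and the documents do not support them.

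- A reader might infer that the arm effect is confounded with city. An arm without a Vaasa cluster is usually a 2/1/0 split, and with two or three Vaasa clusters no arm can be all Vaasa. Any confounding is partial, and its size is unknown. The record software and codes are identical in both cities, which removes a technical source of difference though not a behavioural one. The protocol's own intra-class correlation of 0.02 offers a rough scale. If all between-cluster variance were due to city, with three of 12 clusters in Vaasa, the gap at a 10.5% rate would be sqrt(0.02 x 0.105 x 0.895 / (0.25 x 0.75)), about 10 points. A two-cluster imbalance would then shift an unadjusted contrast by about 5 points. At the 33% rate the figures are about 15 and 8 points. The targeted differences from control are 22.5 and 52.5 points.
- A reader might infer that the analysis ignores baseline or rests on an unadjusted t-test of the intervention effect. It does not say so: adjusted models are planned, and only the covariates are unnamed.
- A reader might call the lost precision free. It is not quite: covariates use degrees of freedom, and any gain from the baseline score comes from the adjustment, not from how lots are drawn.

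The planned adjustment does not fully answer the point. It helps only if city is among the covariates, and even then an unlucky draw inflates the variance.

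**Conclusion.** The point holds as a worthwhile design improvement, not as an error. As described, the draw leaves roughly a one-in-four chance (18% to 32% over the range considered) that control and high-intensity differ by two or more Vaasa clusters out of four. Adjusting for city after the fact multiplies the variance of that contrast by 1.15 on average, and by 2.5 at worst, with three Vaasa clusters.

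These figures rest on 12 clusters, which is the number needed and not a reported count; on equal arms; and on an assumed number of Vaasa clusters after merging. With more clusters the imbalance would tend to be smaller. The effect on the trial's estimate cannot be stated, because neither a city difference nor a baseline-to-follow-up correlation is given.

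**What to change.** Have the chief dentists supply one concealed sequence per city, and draw lots within each city with arm counts fixed as equally as possible. With three Vaasa clusters this gives one per arm. With two to six Vaasa clusters the arms then differ by at most one, although with only two some arm must still go without.

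Optionally, where numbers allow, group the Tampere clusters in threes by baseline audit rate before drawing. This works evenly with nine Tampere clusters but not with eight. Someone other than the allocating investigators should do the grouping, because linking audit data to the sequence would otherwise weaken its concealment.

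Name city, as the stratification factor, and the baseline audit score as covariates in the adjusted generalised linear model already planned. If the full protocol already stratifies the draw, one sentence saying so is enough.

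The cost is two sets of lots instead of one, a sort of existing data if grouping is used, and about two of roughly nine cluster-level residual degrees of freedom. No participants or visits are added. The baseline covariate repays its cost only if its correlation with follow-up exceeds about 0.3.

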### Sample size

There is a scarcity of recent national data regarding the implementation of TUPAC counselling guidelines reported by dental providers. Hence, we conducted our sample size calculations based on population reports collected by the National Institute for Health and Welfare from a random sample (n = 5,000) of Finnish adults [8]. The data showed that 10.5% of surveyed tobacco users who visited the dentist at least once during the past 12 months had received any TUPAC counselling [8]. As our primary aim is to compare the implementation of TUPAC counselling guidelines between control versus two intervention groups, sample size is calculated using the following assumptions: Our aim is to increase the proportion of counselled patients from 10.5% (control) to 33% in the first (low-intensity) intervention group and to 63% in the second (high-intensity) intervention group, as validated by dental record audit. To achieve 80% power, with a two-sided 5% significance level with an estimated intra-class correlation of 0.02, we will need totally 72 participants and 12 clusters with an average of six participants per cluster. Assuming a baseline response rate of 76%, we will need a sample of 95 dental providers.

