### Guidelines on tobacco dependency treatments

The Finnish Medical Society Duodecim produces national Current Care guidelines based on up-to-date evidence to support healthcare decision making in Finland. The guideline for Smoking, Nicotine Addiction, and Interventions for Cessation was published for the first time in 2002 and updated in 2006. The Current Care guidelines for TUPAC counselling recommend a six *A*s approach (Ask, Assess, Account, Advise, Assist, Arrange) [12], which is similar to the five *A*s approach presented by US and other national guidelines [13]. The main principles in TUPAC guidelines include a recommendation that the healthcare provider ask about each patient's tobacco use at least once a year, assess the patient's readiness and willingness to stop, document tobacco use habits (what type of tobacco, quantity, duration), advise the patient to stop tobacco use and instigate supportive measures where necessary, assist and help the patient in his/her attempt to stop tobacco use, and arrange monitoring of progress at follow-up appointments. Historically, however, dental providers, and dentists in particular, have not been routinely involved in the TUPAC counselling. The latest national data show that only 10.5% of daily tobacco users who had visited a dentist during the past year had received advice to quit tobacco use [8]. The gap between guideline recommendation and implementation is evident.

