### Primary outcome measures

The meta-analysis shows that if TUPAC guidelines are implemented, the time used by healthcare providers for counselling is one of the best predictors for counselling success [13]. As our target behaviour will be the implementation of TUPAC guidelines, our primary outcome measures will be (a) whether the TUPAC guideline recommendations are implemented, and (b) if implemented, the estimated time used for the counselling. We will use the electronic dental record (EDR) audit for measuring these outcomes. If the dentist or dental hygienist provides TUPAC counselling, documented procedure codes will give information on the effect counselling may have had. A similar procedure-code documenting system is widely used in dentistry (fillings, extractions, etc.). The codes for TUPAC counselling will be as follows: TI02 = minimal counselling (<3 minutes), TI03 = low-intensity counselling (3 to 10 minutes), and TI04 = higher-intensity counselling (>10 minutes). Categories of intervention duration are based on the meta-analysis, where the estimated odds ratios (ORs) for TUPAC counselling are reported using the same counselling durations (OR = 1.3 for minimal counselling, OR = 1.6 for low-intensity counselling, and OR = 2.3 for higher-intensity counselling) [13]. When multiplying the procedure codes by the estimated ORs and summing the results, we will create one continuous primary outcome. The EDR softwares used in the Vaasa and Tampere health centres are identical (Effica by Tieto Finland, Helsinki) and include the above-mentioned codes for each intervention intensity.

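### The 80% power is derived for a proportion of counselled patients, not for the continuous provider score named as the primary outcome

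*Protocol article*

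**What the plan says.** Three parts of the protocol article bear on this.

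- **Sample size, effect and unit.** The effect is set out as "Our aim is to increase the proportion of counselled patients from 10.5% (control) to 33% in the first (low-intensity) intervention group". The target for the high-intensity arm is 63%, to be confirmed from the dental records. The control rate comes from a population survey, in which "10.5% of surveyed tobacco users who visited the dentist at least once during the past 12 months had received any TUPAC counselling". The error rates and clustering are given as "To achieve 80% power, with a two-sided 5% significance level with an estimated intra-class correlation of 0.02". The result is 72 participants in 12 clusters averaging six, and then "Assuming a baseline response rate of 76%, we will need a sample of 95 dental providers".
- **Participants.** The people invited are the dentists and dental hygienists of the two municipal health centres. The Trial update reports that 73 of 95 took part.
- **Primary outcome measures.** The section begins with two measures: "our primary outcome measures will be (a) whether the TUPAC guideline recommendations are implemented, and (b) if implemented, the estimated time used for the counselling". It then combines them: "When multiplying the procedure codes by the estimated ORs and summing the results, we will create one continuous primary outcome". The weights are 1.3, 1.6 and 2.3 for the three duration bands.

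The Data analysis section plans generalised linear models and modified t-tests for the comparison between arms.

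**The concern.** A power statement is useful only if it describes the quantity that will be tested, in the units that will be counted. Here there are two breaks.

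- **Unit.** The percentages are proportions of patients, but the 72 and the 95 are providers. No number of patients per provider enters the calculation.
- **Endpoint.** The outcome to be tested is a continuous weighted sum, while the calculation is for a binary proportion. Nothing in it fixes the score's spread, the difference sought or the score's clustering.

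What is at stake is interpretation. If the trial shows no difference on the score, the article gives no basis for saying whether a worthwhile difference was likely to be missed. A reader who relies on the 80% would be relying on a figure for a different quantity.

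**Working it through.** **Inputs from the article.** Proportions 0.105, 0.33 and 0.63; two-sided 5%; 80% power; ICC 0.02; 12 clusters of six; 72 participants; 76% response. **Assumption.** The allocation ratio is not stated, so equal arms are taken: 4 clusters and 24 providers per arm. The design effect is 1 + (6 − 1) × 0.02 = 1.10.

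**Step 1. Reproduce the plan's figures.** The inflation reproduces: 72 / 0.76 = 94.7, so 95. For the 72, each provider is taken as one binary observation and

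n per arm = [1.96·√(2·p̄(1−p̄)) + 0.842·√(p₁(1−p₁) + p₂(1−p₂))]² / (p₂ − p₁)²

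For 10.5% against 33%, p̄ = 0.2175, and n = (1.144 + 0.472)² / 0.225² = 51.6, so 52. Multiplied by 1.10 this is 57 to 58, depending on where one rounds. The same formula gives:

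| Contrast | n per arm | × 1.10 | Three arms |
|---|---|---|---|
| 10.5% vs 33% | 52 | 58 | 174 |
| 33% vs 63% | 43 | 48 | 144 |
| 10.5% vs 63% | 12 | 14 | 42 |

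None gives 72. One-sided testing, a continuity correction and multiplicity-adjusted alpha levels do not give it either. The only route found compares 10.5% with 48%, the mean of 33% and 63%, in equal groups: 21.9 × 1.10 = 24.1 per arm, taken as 24, times 3 = 72. The article does not describe that calculation.

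**Step 2. Power on the stated binary inputs.** The effective n per arm is 24 / 1.10 = 21.8, and

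power = Φ{[(p₂ − p₁)·√n − 1.96·√(2·p̄(1−p̄))] / √(p₁(1−p₁) + p₂(1−p₂))}

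For 10.5% against 33% this is Φ{(1.051 − 1.144) / 0.561} = Φ(−0.165) = 43%.

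| Contrast | Normal approximation | t-test on 4 vs 4 clusters (6 df) |
|---|---|---|
| Control vs low | 43% | 35% |
| Low vs high | 51% | 42% |
| Control vs high | 97% | 94% |

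**Step 3. The unit matters.** The factor 1.10 holds for six units per cluster, that is, for providers. If patients were the units, with an assumed 20 per provider, a cluster would hold 120 and the design effect at the same ICC would be 1 + 119 × 0.02 = 3.38. The article's arithmetic belongs to providers and its percentages to patients.

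**Step 4. The score itself.** With no SD, only a standardised difference can be given. For 80% power with 24 per arm,

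d = (1.96 + 0.842)·√(2 × 1.10 / 24) = 2.802 × 0.303 = 0.85 SD

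or about 1.02 SD for a t-test on 4 against 4 cluster means. If the score's ICC were 0.05 or 0.10 (assumed), these become 0.90 or 0.99 SD, and 1.09 or 1.20 SD. At ICC 0.02, power by the normal approximation for an assumed difference of 0.5, 0.65, 0.8 or 1.0 SD is 38%, 57%, 75% or 91%.

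**The case against.** **The basis is related to the outcome.** Component (a), whether the guideline was implemented, is close to binary and is read from the same record audit. This stands, but it does not rescue the figure: the proportion is still among patients while providers are counted, and the article says that the components become one continuous score.

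**Other contrasts do better.** The aim could be read as the control arm against both intervention arms together. With 24 against 48 providers, 10.5% against 48% has about 90% power. A three-group chi-square test has about 91%. Both are fair readings of the binary inputs. They show that the figure depends on a contrast the article does not fix, and neither returns 72: about 56 (18.6 × 3) and 53 would be enough. Treating each provider as one observation is itself an inference.

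**The limits are acknowledged.** The article explains that it used survey data because recent national data were scarce, and its Discussion concedes under-recording in the dental record and a small sample. That is candid, but it does not say what difference in the score the sample can detect.

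**Stronger readings.** A reader might infer three further things that the article does not support.

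- *That the trial is underpowered for its primary outcome.* Without an SD this cannot be shown.
- *That two measures and a composite compete as primary, so no result decides success.* The wording is loose, but the natural reading is two components merged into one outcome.
- *That an intervention adding many brief sessions would look harmful on counselling time.* No separate test of time is planned, and in the summed score each added brief session contributes 1.3.

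**Conclusion.** The point holds in this form: the stated 80% power is for a proportion of counselled patients and is counted in providers, so it does not describe the continuous score that is the primary outcome. Power for that score is undetermined and may be above or below 80%.

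On the article's own binary inputs, the smaller contrast with control has about 43% power and would need about 57 to 58 providers per arm, against 24. Only control against high intensity, among the pairwise contrasts, exceeds 80%. These figures assume equal allocation, one observation per provider and a design effect of 1.10. They are not estimates of power for the score.

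Since all eligible providers were invited and 73 joined, the sample is largely settled. The correction changes how a result can be interpreted more than how many are enrolled.

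**What to change.** 1. State that the composite score, analysed per provider, is the single primary outcome, with (a) and (b) as its components.
2. From the September 2009 record audit, estimate the score's mean, between-provider SD and clinic ICC.
3. Replace the 80% power statement with the difference in the score detectable with the 73 enrolled providers, naming the contrast between arms and the allocation. Show it over a range of ICC values, since an estimate from about a dozen clusters will be imprecise.

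Until then, the 0.85 SD and 1.02 SD given above for ICC 0.02 can serve as reference values.

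The cost is a few hours' analysis of data already held and a change of wording. The downside is that the restated figure may look less favourable than the present 80%.

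### The single 80% power figure does not hold for low intensity versus control: with providers as the unit and equal arms, 72 participants give about 44%

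*Protocol article*

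**What the plan says.** All the ingredients stand in the Sample size section of the protocol article.

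- Comparison: "our primary aim is to compare the implementation of TUPAC counselling guidelines between control versus two intervention groups".
- Assumed rates for control and low intensity: "increase the proportion of counselled patients from 10.5% (control) to 33% in the first (low-intensity) intervention group". The matching target for high intensity is 63%, and the section names the record audit as the check on these rates.
- Error rates and clustering: "To achieve 80% power, with a two-sided 5% significance level with an estimated intra-class correlation of 0.02".
- Result: "we will need totally 72 participants and 12 clusters with an average of six participants per cluster".
- Inflation for response: "Assuming a baseline response rate of 76%, we will need a sample of 95 dental providers".

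The Trial design section gives three arms: investigators will "allocate clusters randomly to (a) control, (b) low-intensity intervention, or (c) high-intensity intervention groups". Neither section states the allocation ratio. The Sample size section does not say which comparison the 80% belongs to, does not exempt the low-intensity arm from it, and does not say how many patients per provider enter the calculation.

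**The concern.** One power figure is attached to two comparisons with very different assumed effects: 22.5 percentage points for low intensity against control (33 − 10.5) and 52.5 points for high intensity against control (63 − 10.5). One sample size cannot give 80% power for both. Twenty-four providers per arm looks ample for the larger difference and far too few for the smaller.

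At stake is how a null low-intensity result would be read. Beside an unqualified 80%, it invites the conclusion that the low-intensity intervention does not work. If the true power is below one half, a non-significant result is more likely than not even when the assumed effect is real.

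**Working it through.** **Inputs.** From Sample size: control 0.105, low intensity 0.33, high intensity 0.63; two-sided alpha 0.05 (z = 1.960); power 80% (z = 0.842); intra-class correlation 0.02; 72 participants, 12 clusters, six per cluster. From Trial design: three arms. Two assumptions are needed that the plan does not state: equal arms, and one yes/no outcome per provider.

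**The plan's own figures.** 12 × 6 = 72, and 72/0.76 = 94.7, which rounds up to 95. Both agree with the text, and the second shows that the 72 are providers.

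**Effective size.** 72/3 = 24 per arm, that is, four clusters of six. Design effect = 1 + (6 − 1) × 0.02 = 1.10. Effective n = 24/1.10 = 21.8 per arm.

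**Required size.** With p̄ the mean of the two rates, the pooled-variance formula is

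n = [1.960 √(2p̄(1 − p̄)) + 0.842 √(p₀(1 − p₀) + p₁(1 − p₁))]² / (p₁ − p₀)²

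- Low versus control: p̄ = 0.2175. The terms are 1.960 × 0.5834 = 1.1435 and 0.842 × 0.5613 = 0.4724. n = 1.6159²/0.225² = 51.6; × 1.10 = 56.7, so about 57 per arm and 3 × 57 = 171 in total.
- High versus control: p̄ = 0.3675. The terms are 1.960 × 0.6818 = 1.3364 and 0.842 × 0.5719 = 0.4813. n = 1.8177²/0.525² = 12.0; × 1.10 = 13.2 per arm.

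Neither result is 24 per arm.

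**Power at the planned size.** Power = Φ{[(p₁ − p₀)√n − 1.960 √(2p̄(1 − p̄))] / √(p₀(1 − p₀) + p₁(1 − p₁))} with n = 21.8, √n = 4.671.

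- Low versus control: (0.225 × 4.671 − 1.1435)/0.5613 = −0.165, so 43.5%.
- High versus control: (0.525 × 4.671 − 1.3364)/0.5719 = 1.951, so 97%.

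**Sensitivity of low versus control, one outcome per provider.**

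| Variation | Power |
|---|---|
| No clustering at all | 47% |
| Unpooled variance | 46.5% |
| Arcsine | 46% |
| Fisher exact, 22 to 24 per arm | 33–38% |
| t-test on cluster values, 6 df | 35% |
| One-sided 5% | 56% |
| Best unequal split of 12 clusters, at least two per arm | about 54% |
| All 72 placed in these two arms | 60% |

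None reaches 80%.

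**If patients were the unit.** With k patients per provider and only a clinic-level correlation of 0.02, effective n per arm = 24k/[1 + (6k − 1) × 0.02].

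- k = 2: 48/1.22 = 39.3, power 68%.
- k = 3: 72/1.34 = 53.7, power 82%.

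The plan states no k, and this calculation ignores any correlation among patients of the same provider.

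**Where 72 may come from.** A comparison of 10.5% with 48%, the average of 33% and 63%, needs 21.9 × 1.10 = 24.1 per arm, close to the stated 24. This is a guess at the origin; the article does not describe such a calculation.

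**The case against.** The strongest objection concerns the unit. The 44% requires one binary outcome per provider. The Sample size section expresses its rates per patient and refers to the record audit, and the Primary outcome measures section sums weighted procedure codes into a continuous score. With several patients per provider, power for low versus control could exceed 80%, as the k = 3 case shows. This stands as a limit on the figure: 44% follows from counting as the plan counts and is not the established power of the trial. It does not rescue the paragraph, which supplies no number of patients and no provider-level correlation and works in providers from the cluster size to the final 95.

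A second objection is that the 80% may refer to another test. The aim is worded as control against two groups, without saying each. But a three-group chi-square test has 91% power at this size, control against both interventions combined 90%, and high versus control 97%. None of these yields 72 as the size needed for 80%, and the text does not confine its claim to any of them.

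Third, the Discussion concedes that the sample is fairly small and that more participants would add power. That is fair warning in general terms, but it neither withdraws the 80% nor identifies the comparison that falls short.

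Three stronger readings are tempting and are not supported.

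- A reader might infer that high versus low intensity is also a failed power claim. Neither the Sample size nor the Data analysis section claims 80% for that contrast.
- A reader might add a shortfall from loss after baseline. The article gives no loss rate to calculate from.
- A reader might conclude that high versus control should become the only confirmatory test. That is a design preference and would demote part of the stated primary aim.

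**Conclusion.** The concern holds in a limited form. On the printed inputs, with the provider as unit and three equal arms, 72 participants give about 44% power for low intensity versus control, against the stated 80%, and about 97% for high intensity versus control. The low-intensity comparison would need about 57 per arm, about 171 in total. The shortfall does not hinge on the choice of formula or on the split of clusters.

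The figure rests on equal allocation and one binary outcome per provider, neither of which is stated. Because patient rates are combined with a provider count, the documents do not support the stronger statement that the trial as analysed has 44% power. They do support saying that the single 80% is not delivered for low versus control as calculated, and that the unit and the contrast behind it must be stated.

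**What to change.** In the Sample size section, replace the single 80% statement with power for each comparison with control, naming the contrast, the allocation ratio and the unit of analysis.

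- If there is one binary outcome per provider and the arms are equal: state about 44% for low versus control and about 97% for high versus control.
- If patients are the unit: state the assumed number of patients per provider and the intra-class correlations at clinic and provider level, then recalculate both figures.

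In either case, report low versus control with its confidence interval. While its power is well below 80%, say plainly that a non-significant result there is not evidence of no effect.

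This is a change of wording plus one recalculation. It needs no extra participants; the 73 reported in the Trial update can stand. The cost is a less favourable power statement for one of the two comparisons.
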